# Methods

## Study design

This study will be a prospective monocentric randomized controlled trial. Patients will be randomly assigned to the one of the two groups (EEG-guided with BIS *versus* standard of care – SOC). Processed EEG (BIS) will be monitored in both groups but information from those monitors will only be available for the EEG-guided group to guide hypnotic drugs’ administration. All other aspects of anesthesia will be the same between the groups, especially concerning the management of nociception and blood pressure.

## Subject population

All consecutive patients ≥ 70 years old who are scheduled for major gynecologic, abdominal, urologic, thoracic or orthopedic surgery and seen for assessment by internal medicine and/or anesthesiology at the preoperative clinic (CIEPC).

### Inclusion criteria

- Patients 70 years of age or older,
- Major gynecologic, abdominal, urologic, thoracic or orthopedic surgery via laparoscopy or laparotomy under general anesthesia - with or without concomitant use of regional or neuraxial anesthesia -,
- Expected anesthesia time of more than 60 minutes,
- Seen for assessment by internal medicine and/or anesthesiology at the preoperative clinic (CIEPC)

### Exclusion criteria

- Known diagnosis of dementia or other neurological, psychiatric, developmental or medical condition that resulted in documented severe cognitive impairment,
- Emergency surgery,
- Significant auditory or visual impairment that precludes participation in cognitive testing,
- Known allergy or intolerance or other medical condition that precludes the use of prescribed general anesthesia protocol for this study,
- Inability to communicate in French or English.

### Recruitment

All patients will be assessed and recruited by internal medicine and/or anesthesiology from the preoperative clinic (CIEPC) in collaboration with the research team for this study, informed of the study parameters, and provided a consent form to be signed. A total of 314 patients (157 per group) will be included in the study (see below). We estimate an inclusion rate of 3 to 5 patients per week (study duration for inclusions 2 years). In order to avoid missing data, we will conduct telephone interviews for cognitive assessment of patients once they return home.

## Research plan and timeline

Patients will be screened at the preoperative clinic. The day of the surgery (D0), after signing the consent form, patients will undergo the inclusion visit. Cognitive assessment will be performed using the MoCA and verbal fluency tests by a trained research team. Patients will also be screened for depression and frailty. The patient will then be randomized in the EEG-guided or SOC group.

Postoperative visit will be performed at postoperative days 1 and 2 (D1 and D2). Cognitive assessments will be performed using MoCA and verbal fluency tests. Patients will also be screened for postoperative delirium.

Once patients return home, phone interviews will be done at D7, D15, D30 and D90. Cognitive assessments will be performed using the telephone version of the MoCA (T-MoCA) and verbal fluency tests. Quality of recovery will be evaluated at D30 and D90 using the QoR-15 questionnaire.

T-MoCA and T-MoCA part of the MoCA as well as verbal fluency will be used to establish cognitive trajectories of the two groups.

The 3 versions of the MoCA will be alternately and randomly used to limit learning effect.

Estimated time for each visit is approximatively 45 minutes. The study timeline used tests and expected cognitive trajectories are presented in figure 1.

All the tests are provided in the references and detailed below. These tests are also attached in the annexes in French and in English.

[figure not shown]

**Figure 1. Study timeline, tests and expected cognitive trajectories**. *MoCA: Montréal Cognitive Assessment; PHQ-9: Patient Health Questionnaire 9; CFS: Clinical Frailty Scale; EEG: electroencephalograph; SOC: Standard of Care; CAM: Confusion Assessment Method; QoR: Quality of Recovery; T-MoCA: Telephone MoCA.*

## Anesthesia Protocol

### General

All patients will undergo general anesthesia with the following: induction with IV slow boluses of lidocaine to numb the vein, propofol 1.5mg.kg^-1^, remifentanil 1µg.kg^-1^ over 30 seconds, rocuronium 0.8 mg.kg^-1^. We will proceed to orotracheal intubation when response to neuromuscular stimulation of the adductor pollicis has reached 5% of the original T4 amplitude. The maintenance of anesthesia will depend on sevoflurane to reach [0.8–1.2] minimal alveolar concentration (MAC; MAC adjusted to the patient’s age) in the control group, and to achieve a BIS of [40-60] in the EEG-guided group (see below). The remifentanil infusion will start at 0.02 µg.kg^-1^.min^-1^ and increase by 0.02 µg.kg^-1^.min^-1^. If the NOL index is > 25 for more than 1 min, we will administer one bolus of 0.3 µg.kg^-1^. The maximum remifentanil rate allowed intraoperatively will be 0.3 µg.kg^-1^.min^-1^. This rate will be decreased by step of 0.02 µg.kg^-1^.min^-1^ if the NOL index is < 5 for more than 3 minutes (for a minimum rate of 0.02 µg.kg^-1^.min^-1^). We will administer intravenous boluses of rocuronium as needed for the response to TOF stimulation to stay below 2/4.

Baseline mean arterial blood pressure (MAP) will be defined as the average of 3 consecutive values taken 1 min apart and determined before the induction of general anesthesia. Intravenous (IV) infusion of phenylephrine will start at 0.2 µg.kg^-1^.min^-1^ and adjusted to maintain +/- 20% of the baseline values of the pre-anesthesia MAP. Benzodiazepines or ketamine will not be used, and patients will receive standard prophylaxis against postoperative nausea and vomiting (avoiding haloperidol).

Remifentanil and phenylephrine infusions will be discontinued when the skin is closed. At the same time, muscle relaxation will be antagonized using neostigmine 0.04 mg.kg^-1^ and glycopyrrolate 0.01 mg.kg^-1^, and bolus of ondansetron 4mg and hydromorphone 0.006 µg.kg^-1^ administered. Sevoflurane will be discontinued when the wound dressing is completed, and patients will be extubated in the operating room, then transferred to the post-anesthesia care unit (PACU).

Hydromorphone PCA (or SC hydromorphone if patient is not a candidate for PCA) for postoperative pain scores < 4/10, or PCEA (if an epidural was placed) is started in PACU. All patients will be managed according to ERAS (Enhanced recovery after surgery) principles. All anesthesia related side effects and quality of analgesia and, rehabilitation will be evaluated for 48h (see below).

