# Publication Plan

Publication of the study protocol will be submitted once approved by the Ethical committee to the journal PLoS ONE.

Publication of the results of the present study will be proposed to JAMA or Lancet, and if not accepted to ANESTHESIOLOGY or British Journal of Anaesthesia.

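### The hydromorphone bolus ordered for every patient at skin closure is written as 0.006 µg/kg (0.42 µg at an assumed 70 kg); the unit is probably wrong by a factor of 1000

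*Protocol*

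**What the plan says.** Section D.4.1 (General, under Anesthesia Protocol) sets one regimen for both arms, opening with "All patients will undergo general anesthesia with the following". At the end of surgery it states: "Remifentanil and phenylephrine infusions will be discontinued when the skin is closed". At that same moment "muscle relaxation will be antagonized using neostigmine 0.04 mg.kg^-1^ and glycopyrrolate 0.01 mg.kg^-1", together with a "bolus of ondansetron 4mg and hydromorphone 0.006 µg.kg^-1^ administered".

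Earlier in the section, the intraoperative remifentanil rescue dose is given: "If the NOL index is > 25 for more than 1 min, we will administer one bolus of 0.3 µg.kg^-1".

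The section then moves to the recovery room (PACU), where hydromorphone by PCA or subcutaneously, or epidural analgesia, is started; no hydromorphone dose is given there. The Protocol summary also names hydromorphone only by route. The skin-closure bolus is therefore the only hydromorphone dose in the document.

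On publication, section K states: "Publication of the study protocol will be submitted once approved by the Ethical committee to the journal PLoS ONE".

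**The concern.** A weight-based dose of a few thousandths of a microgram per kilogram is out of scale with everything else in the regimen, and it sits beside three drugs in milligrams. That pattern suggests a unit slip rather than an intended dose.

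The line is an instruction, not background. It applies to every one of the 314 planned patients, all aged 70 or over, at the point where the only other opioid in the regimen is being stopped. Followed literally, it leaves a near-zero bolus until PACU analgesia starts. If clinicians notice and substitute their own dose, the regimen delivered is no longer the one written. That sits badly with the Study Rationale (B.2), which regards opioid use as a possible source of bias for the cognitive outcome and promises strict control of intraoperative opioids. If the protocol is published uncorrected, the wrong unit goes with it.

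**Working it through.** **Inputs**

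- Hydromorphone bolus: 0.006 µg/kg (D.4.1).
- Remifentanil: rescue bolus 0.3 µg/kg, induction bolus 1 µg/kg, minimum infusion 0.02 µg/kg/min (D.4.1).
- Other weight-based boluses in D.4.1: propofol 1.5 mg/kg, rocuronium 0.8 mg/kg, neostigmine 0.04 mg/kg, glycopyrrolate 0.01 mg/kg. Ondansetron is a flat 4 mg.
- Body weight: not in the protocol. Assumed 70 kg, range 50 to 100 kg.

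The protocol derives no total hydromorphone dose, so there is no figure of its own to reproduce.

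**Step 1. Dose given.** Dose = dose per kg × weight.

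| Assumed weight | As written (0.006 µg/kg) | If mg/kg was meant (0.006 mg/kg) |
|---|---|---|
| 50 kg | 0.30 µg | 0.30 mg |
| 70 kg | 0.42 µg | 0.42 mg |
| 100 kg | 0.60 µg | 0.60 mg |

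The columns differ by exactly 1000. As written, the dose reaches 1 µg only at 1 / 0.006 = 167 kg.

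**Step 2. Scale against the other boluses in the section, all in µg/kg.**

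| Drug | µg/kg |
|---|---|
| Propofol | 1500 |
| Rocuronium | 800 |
| Neostigmine | 40 |
| Glycopyrrolate | 10 |
| Remifentanil, induction | 1 |
| Remifentanil, rescue | 0.3 |
| Hydromorphone, as written | 0.006 |
| Hydromorphone, if mg/kg | 6 |

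The next smallest bolus is the remifentanil rescue dose, and 0.3 / 0.006 = 50. Against the induction dose the ratio is 1 / 0.006 = 167. The written bolus equals the mass of remifentanil delivered in 0.006 / 0.02 = 0.3 min, or 18 seconds, at the lowest permitted infusion rate. These ratios compare mass, not potency. They show how far the figure lies from the rest of the regimen, not how strong the dose is.

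**Step 3. Units of the drugs given at the same moment.** Neostigmine and glycopyrrolate are in mg/kg and ondansetron is in mg. Hydromorphone alone is in µg. Changing that one unit to mg gives 6 µg/kg, inside the range of the other boluses.

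**Step 4. Could the text extraction have changed the unit?** Unlikely. The same section shows µg for remifentanil and phenylephrine and mg for propofol, rocuronium, neostigmine and glycopyrrolate, all plausibly. A misreading confined to this one unit would be an odd coincidence.

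**The case against.** The strongest objection is that the document does not prove the unit wrong. It gives no reference dose, maximum or concentration for hydromorphone. A mass comparison between two different opioids says nothing about potency. The neighbouring mg drugs belong to other classes, and the one other opioid in the section is itself in µg. The number could be wrong as well as the unit. All of this is fair, and it is why the finding is worded as probable and the intended dose is left to be confirmed. It does not make 0.006 µg/kg a sensible order.

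It can also be said that this is a typing slip, not failed arithmetic; that it errs toward too little opioid rather than too much; that an anesthesiologist would be expected to query a 0.42 µg bolus; and that PACU analgesia follows soon, with an epidural in some patients. These points reduce the practical risk. They do not correct the text, and an opioid order should not depend on the reader noticing a thousand-fold discrepancy.

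Two narrower points stand. Publication of the wrong unit is a possibility, since it could be caught first. And recruitment status is not known from the document: the Study Timetable (J.2) expected inclusion to end in spring 2023, so notifying the operating-room team matters only if patients are still being treated.

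**Conclusion.** The concern holds. The protocol orders a single hydromorphone bolus for all patients that amounts to 0.30 to 0.60 µg over assumed weights of 50 to 100 kg, and nothing elsewhere in the document corrects it. Reading the unit as mg/kg gives 0.30 to 0.60 mg and accounts for the anomaly with one change. That reading is an inference from the surrounding units and the scale of the regimen. That a sub-microgram hydromorphone dose has negligible effect is general pharmacology, not something the protocol states.

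The order is identical in both arms, so it does not bias the group comparison, and the sample size and analysis methods do not depend on it. Whether the bolus counts toward the secondary endpoint of intraoperative opioid consumption is not stated, so no effect on that endpoint is claimed. The point should be fixed because it is a dosing instruction for elderly patients, not because it threatens the trial's inference.

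**What to change.** Have the responsible clinicians and pharmacy confirm the intended hydromorphone dose. Then correct the unit in D.4.1, probably to 0.006 mg/kg, by a one-line amendment before the protocol is used further or published. If patients are still being treated, notify the operating-room team. If enrolment is complete, make the correction in the protocol record and in any publication, and state the dose actually given. The cost is one line of text and a short notice; design, sample size and analysis are unchanged.

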### Monitoring

Routine monitoring of patients will be the same for both groups and will include 5 leads ECG, non-invasive blood pressure, pulse-oximetry and a temperature probe. We will record all data using the Dräger Perseus A500 (Dräger Medical, Lübeck, Germany) monitor and send all anesthesia related data electronically to a research computer for anonymized storage and further analysis.

We will place the NOL index finger probe (PMD-200™ device, Medasense Biometrics Ltd, Ramat Gan, Israel) and the bilateral cerebral regional oximetry rSO_2_ (Invos™, Medtronic, Canada) (both are available to the anesthesiologist for both groups throughout the entire anesthesia).

Bilateral BIS^TM^ EEG sensor (Medtronic, Canada) will be placed on the forehead for all patients. For the SOC (standard of care) group, only the electrode status display will be available; the rest of the data will be hidden by a dark screen – and unavailable to the anesthesiologist during the anesthesia.

### Intervention

In the EEG-guided group, the information provided by the BIS^TM^ monitor will guide the volatile anesthetic administration in the EEG-guided group. Sevoflurane end-tidal anesthetic concentration (ETAC) will be adjusted to maintain a BIS value between 40 and 60, a Suppression Ratio (SR; % of time with suppressed brain electrical activity) at 0%, a direct EEG display without any suppression time and a spectrogram (DSA or density spectral array) with most of the EEG wave frequency within the Alpha (8-12Hz), Theta (4-8Hz) and Delta (0.5-4Hz) frequencies.

In the non-EEG-guided group, the MAC of sevoflurane (adjusted to age) will be used to guide the intraoperative anesthesia delivery and MAC will be kept between 0.8 and 1.2.

## Randomization and blinding

A randomization list will be electronically made and followed for the 314 subjects. An envelope containing the study group will be given to the anesthesiologist in charge once the patient will be in the operating room and be opened after the inclusion visit to limit contamination bias. All patients and researchers assessing outcomes and adverse events will be blinded to randomization assignments.

## Measurements

### Cognitive Assessments

#### The Montreal Cognitive Assessment tool

Participants will undergo preoperative cognitive assessment to establish a baseline, then postoperatively to assess changes from that baseline. We will perform preoperative assessment the morning of the scheduled surgery and postoperative assessments on days 1, 2, 7, 15, 30 and 90.

All cognitive assessments will use the Montreal Cognitive Assessment (MoCA) tool. The MoCA takes roughly 10 min to administer and covers eight cognitive domains. It was originally designed as a screening tool to detect mild cognitive impairment (MCI)^46^ but it is also used in clinical and research assessment of a variety of neurological and cognitive pathologies. A score below 26 is considered positive for cognitive impairment. It has three versions, allowing for retesting with low risk of learning between assessments. The telephone version of the MoCA (T-MoCA) is scored on a scale of 0 to 22 and corresponds to the MoCA and excludes the visuospatial/executive and naming component. The T-MoCA has proved to be a reliable method to assess MCI after stroke^47^ and has been used to explore cognitive functions after major non-emergent surgery^27^. As mentioned in the exclusion criteria, patients with preoperative documented diagnosis of dementia or other neurological, psychiatric, developmental or medical condition that resulted in documented severe cognitive impairment will not be included in the proposed study. Nevertheless, in the event that we diagnose a preoperative neurocognitive disorder (i.e., preoperative MoCA <26), patients will still be included in the study. At the end of the follow-up (at 3 months postoperatively), patients will be informed of the possibility of an incipient neurocognitive disorder and referred to a neuropsychologist for a more thorough neuropsychological test battery. Subgroup analyses are planned for patients with preoperative neurocognitive impairment

In our previous feasibility study, we encountered difficulties administering MoCA to patients who had left the hospital. So, we chose to use MoCA for in-hospital cognitive assessments and the T-MoCA once patients returned home. The MoCA scores will be used for the primary endpoint assessment – pre-anesthesia versus at H24 after surgery- and T-MoCA scores will be used to establish the cognitive trajectories up to 3 months after general anesthesia for major surgery in this elderly population.

#### Verbal Fluency

Testing verbal fluency tests requires a participant to generate as many words as possible within set times and parameters - phonemic verbal fluency: *e.g.,* words that start with the letter f, categorical verbal fluency: *e.g.,* names of animals. These verbal tasks evaluate lexical access but also assess sustained attention and memory. These tests can be completed in person or over the phone – both have proven reliable means of administering the test in both French and English^48-51^ – and are excellent tools to assess a variety of cognitive impairments across many disorders (MCI, Alzheimer Dementia, traumatic brain injury, Parkinson Disease).

#### Z Scores and Definition of Neurocognitive Disorders (NCD)

We will calculate Z scores for individual tests - (Verbal fluency, MoCA, T-MoCA) at each testing time point with the mean and standard deviation (SD) of baseline tests of all patients - in the following way:

$$Z_{test}=\frac{x_{test}-\mu_{test baseline}}{\sigma_{test baseline}}$$

where $x$ corresponds to individual test value, $\mu$ and $\sigma$ correspond to test mean and SD of all patients at baseline respectively.

We will use MoCA Z scores (or T-MoCA depending on the testing time point) to define NCD. Neurocognitive disorders will be classified as mild or major^12,15^:

- **No NCD**: a decrease in Z score < 1 SD,
- **Mild:** a decrease in Z score ≥ 1 SD,
- **Major:** a decrease in Z score ≥ 1.96 SD.

| Z score decrease | Postoperative days 1,2,7,15, 30 and 90 |
| --- | --- |
| < 1 SD | No NCD |
| ≥ 1 SD and < 1.96 SD | Mild NCD |
| ≥ 1.96 SD | Major NCD |

### Other Assessments

#### Preoperative Assessment of Depression and Frailty

We will pre-screen for symptoms of severe depression and extreme fragility at preoperative enrollment, to ensure cognitive impairment is not related these two conditions. We will use the Patient Health Questionnaire 9 (PHQ-9) to detect severity of depression^52^ and the Clinical Frailty Scale 2.0^53^ (CFS) to assess frailty. Both screening tools are easy to use for clinicians, are validated, and available in French^54,55^.

#### Delirium Assessment

We will administer the Confusion Assessment Method (CAM) on postoperative days 1 and 2. The CAM is a validated assessment tool for the diagnosis of delirium^56^ and is based on the diagnostic criteria for delirium from the Diagnostic and Statistical Manual of Mental Disorders (DSM). The cognitive testing on postoperative days 1 and 2 will consist of basic orientation questions and a sustained attention task (stating the months of the year backwards). If the CAM yields a positive diagnosis, we will administer a subsequent test, the CAM-S which assesses the severity of delirium. In the case of persistent mechanical ventilation after surgery in the ICU, we will administer the Intensive Care Unit version of the CAM (CAM-ICU)^57^.

#### Postoperative Assessment of Quality of Life

We will perform the Quality of Recovery-15 (QoR-15) interview will be performed at postoperative day 30 and 90 to explore quality of life after anesthesia and surgery, and to assess differences between groups. This is a validated shorter version of the QoR-40 with only 15 items^58^.

### Endpoints

#### Primary Endpoint

- Incidence of major NCD at postoperative day 1.

#### Secondary Endpoints

- The incidence of major NCD at postoperative day 2, 7, 15, 30 and 90
- The evolution over time in cognitive assessment scores defining cognitive trajectories,
- The incidence of postoperative delirium during hospital stay,
- The total intraoperative consumption of volatile anesthetics, opioids and vasopressors over surgery time
- The incidence of intraoperative hypotension,
- The incidence of cerebral hypoxemia,
- The cumulative burst suppression duration and low BIS values duration during anesthesia,
- The incidence of awareness,
- The difference between quality of recovery scores between groups.

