Patients will be randomized (1:1) to receive EEG guided anesthesia versus standard of care. Information provided by the BIS^TM^ (Medtronic, Canada) monitor will guide the volatile anesthetic administration in the EEG-guided group to maintain a BIS value between 40 and 60, a Suppression Ratio (SR; % of time with suppressed brain electrical activity) at 0% or the closest, a direct EEG display without any suppression time and a spectrogram (DSA or density spectral array) with most of the EEG wave frequency within the Alpha (8-12Hz), Theta (4-8Hz) and Delta (0.5-4Hz) frequencies. In the standard of care group, the age-adjusted Minimum Alveolar Concentration (MAC-age) of sevoflurane will be kept at [0.8-1.2] MAC.

Cognitive Assessment

Participants will undergo cognitive assessment preoperatively to establish a baseline and then postoperatively to assess change from that baseline at postoperative days 1, 2, 7, 15, 30 and 90.

- The MoCA or the telephone version of the MoCA (T-MoCA) will be administered at each time point depending on patient location (hospital / home).
- Verbal fluency including phonemic and categorical fluency will be administered at each time point
- The Confusion Assessment Method (CAM) will be used to diagnose postoperative delirium at postoperative days 1 and 2.
- The Quality of Recovery-15 (QoR-15) questionnaire will be used at postoperative day 30 and 90 to explore quality of life after anesthesia and surgery.

Endpoints

An individual reduction of the MoCA score (or T-MoCA depending on testing time point) ≥ 1.96 standard deviation calculated on overall population preoperative mean will define major NCD.

The primary endpoint will be:

- The incidence of major NCD at postoperative day 1.

Secondary endpoints will include:

- the incidence of major NCD at postoperative day 2, 7, 15, 30 and 90
- evolution in cognitive assessment scores over time defining patients’ trajectories,
- the incidence of postoperative delirium during hospital stay,
- the total intraoperative consumption of volatile anesthetics, opioids and vasopressors over surgery time,
- the incidence of intraoperative hypotension
- the incidence of cerebral hypoxemia
- the incidence of awareness,
- cumulative burst suppression duration and low BIS values duration during anesthesia
- the difference between quality of recovery scores between groups.

Tertiary endpoints will include:

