## Secondary Objectives

Secondary objectives are to investigate the effect of EEG-guided anesthesia on:

- neurocognitive disorders (NCDs) at postoperative day 2, 7, 15, 30 and 90,
- patients’ perioperative cognitive trajectories,
- postoperative delirium,
- intraoperative consumption of volatile anesthetics, opioids and vasopressors,
- intraoperative hypotension (number of interventions to treat hypotensive events),
- cerebral hypoxemia (assessed by cerebral oximetry),
- cumulative burst suppression duration and cumulative low processed EEG (BIS) values duration during anesthesia,
- risk of awareness,
- postoperative quality of life / recovery outcomes (including length of hospital stay and surgical complications).

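### The delirium endpoint covers the whole hospital stay, but delirium is assessed only on postoperative days 1 and 2

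*Protocol*

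**What the plan says.** **The endpoint.** Protocol, Secondary Endpoints (D.6.3.2), lists "The incidence of postoperative delirium during hospital stay". The endpoint list in the protocol summary repeats it: "the incidence of postoperative delirium during hospital stay". Both windows run to discharge.

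**The assessment.** Protocol, Delirium Assessment (D.6.2.2), states: "We will administer the Confusion Assessment Method (CAM) on postoperative days 1 and 2". The summary, under Cognitive Assessment, agrees: "The Confusion Assessment Method (CAM) will be used to diagnose postoperative delirium at postoperative days 1 and 2". Research plan and timeline (D.3) places the in-hospital follow-up visits, and the delirium screening done at them, on the same two days.

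**Later contacts.** The same section continues: "Once patients return home, phone interviews will be done at D7, D15, D30 and D90". The tests named for those contacts are the telephone MoCA, verbal fluency and, at D30 and D90, the QoR-15.

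**Length of stay.** The protocol sets no limit on the stay and gives no expected value. Secondary Objectives (C.2) treats it as something to be compared: "postoperative quality of life / recovery outcomes (including length of hospital stay and surgical complications".

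**The concern.** An incidence claimed for a period needs observation over that period. Here the label extends to discharge, while planned observation stops after day 2. A patient who remains in hospital and first becomes delirious on day 3 or later would be recorded as free of delirium for the entire stay.

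Delirium is a named secondary objective, so the trial intends to draw a conclusion about it. If the label stays, that conclusion, whether a difference or no difference, will be stated for days on which nobody looked. A later analysis plan cannot repair this, because it cannot supply assessments that were not made. The endpoint and the schedule are both fixed in this document, and they disagree.

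**Working it through.** The check is mainly a comparison of passages, because the protocol gives no figure for delirium in this trial.

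**Step 1. Set the two windows side by side.**

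| Item | Window | Where |
|---|---|---|
| Delirium endpoint | To discharge | Summary; Secondary Endpoints |
| CAM | Days 1 and 2 | Summary; Research plan and timeline; Delirium Assessment |

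The windows coincide only for patients discharged by day 2.

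**Step 2. Look for anything that extends ascertainment past day 2.**

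- *CAM-S* grades severity after a CAM that is already positive. It finds no new cases.
- *CAM-ICU* is a version for one group: "In the case of persistent mechanical ventilation after surgery in the ICU, we will administer the Intensive Care Unit version of the CAM (CAM-ICU". No days are given for it, and it does not reach ward patients.
- *Review of side effects, analgesia and rehabilitation* lasts 48 h (Anesthesia Protocol, General). It names no delirium instrument and ends at about the same point.
- *Contacts at D7 to D90* measure cognition and recovery. No delirium instrument is listed.
- *Data Collection Procedures* (E.1) covers monitor data and events of anesthesia and surgery. It describes no chart review or ward reporting of delirium.

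Nothing in the protocol closes the gap.

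**Step 3. Is a stay beyond day 2 foreseeable?** Patients are 70 or older and have major abdominal, thoracic, urologic, gynecologic or orthopedic surgery (Inclusion criteria). The summary chooses between the MoCA and its telephone version at each time point according to whether the patient is in hospital or at home, so the plan does not assume that everyone is home after day 2. How many stay longer is not stated.

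**Step 4. Direction of the error.** Take as reference the count that the same instrument would give if it were continued to discharge. Further assessments can add positive patients but cannot remove one. The day 1 and 2 count is therefore at most equal to the in-hospital count.

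**Step 5. Size of the error.** Let *s* be the share of patients with in-hospital delirium who are detected on day 1 or 2. Then

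reported incidence = *s* × in-hospital incidence,

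and, if *s* is the same in both arms,

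reported risk difference = *s* × in-hospital risk difference.

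The protocol gives no value for *s*, no expected stay and no delirium rate for this population. Its Epidemiology section cites only a literature range of 5% to 50%. Purely to show how the relation works, assume in-hospital rates of 20% and 12%:

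| Assumed *s* | Reported rates | Risk difference |
|---|---|---|
| 1.0 | 20% vs 12% | 8.0 points |
| 0.8 | 16% vs 9.6% | 6.4 points |
| 0.6 | 12% vs 7.2% | 4.8 points |

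Every input in this table is an assumption. It is not an estimate of the shortfall in this trial.

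**Step 6. Is the sample size touched?** The stated 282 rests on major NCD at day 1, 15% versus 5%, two-sided α 0.05 and 80% power. With pooled variance and no continuity correction:

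n per arm = [1.960 × √(2 × 0.10 × 0.90) + 0.842 × √(0.15 × 0.85 + 0.05 × 0.95)]² / 0.10² = (0.8315 + 0.3521)² / 0.01 ≈ 140.1, rounded up to 141.

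Twice 141 is 282, and 282 / 0.90 = 313.3, rounded up to 314. Both figures reproduce, and neither depends on delirium.

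**The case against.** The strongest reply is that this is a loose label and not a failed endpoint. The summary gives the CAM days and the endpoint together, so an attentive reader can see what is measured. Patients discharged by day 2 have no gap. Laparoscopic surgery qualifies, anesthesia need only exceed 60 minutes, ERAS principles apply to everyone and the D7 contact is planned by telephone, so stays of a week cannot be presumed. CAM-ICU has no stated days and might run longer for ventilated patients. The endpoint is one of nine secondary items.

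Most of this stands, and it limits the point. It does not remove the disagreement for ward patients who stay beyond day 2.

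A reader might also infer more than the document supports:

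- *A bias between arms, because length of stay may differ by group.* The CAM days are fixed and identical in both groups, and Randomization and blinding (D.5) blinds the outcome assessors. A longer stay brings no extra planned CAM.
- *A numerical undercount.* This needs a length of stay, an onset distribution and a true rate for this trial, and the protocol supplies none of them.
- *Contamination from unblinded chart review.* No such review is described.
- *Misleading comparison with trials that assessed the whole stay.* The protocol does not give other trials' delirium windows.

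**Conclusion.** The endpoint is wrong as written. Its window is the hospital stay, the observed window is postoperative days 1 and 2, and nothing in the protocol bridges the two. For patients who remain in hospital after day 2, the reported figure can only understate in-hospital incidence. This rests on reading the assessment schedule as complete. An unstated ward procedure, or CAM-ICU use continuing past day 2, would narrow the gap, but neither is in the document.

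The size of the understatement is unknown and cannot be derived here, and no distortion of the comparison between arms is shown. The consequence is confined to what may be concluded about one secondary endpoint.

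**What to change.** In the summary's endpoint list and under Secondary Endpoints (D.6.3.2), restate the item as: *incidence of postoperative delirium (CAM or CAM-ICU positive) on postoperative day 1 or 2*. Limit any conclusion on delirium to that window.

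This changes wording only. It needs no extra visits or data and leaves the primary endpoint, the sample size and patient care untouched. The price is a narrower claim. If the sponsor wants to keep the in-hospital claim, the protocol would have to describe how delirium is ascertained up to discharge, which would mean additional data collection. The denominator and the handling of a missed assessment can be left to the statistical analysis plan.
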